#### Monitoring

The research team is responsible for monitoring the study. At each supervised training session, participants will be asked if they have had any changes during the course of their activities, in addition to being monitored with parameters, as described previously, that may be implied in interruption of the activity or withdrawal of the subject from the PR program.

#### Statistics analysis

The Kolmogorov-Smirnov test will be performed to analyze sample normality, and two-way ANOVA followed by a Bonferroni post hoc test will be used to compare the differences among the groups. Data will be analyzed using the GraphPad Prism software version 5.0 (GraphPad Software Inc., San Diego, CA, USA). The significance level was set at 95% (*p* ≤ 0.05).

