The literature describes two modalities of respiratory muscle training: isocapnic voluntary hyperpnea, which consists of a training that requires the individual to perform voluntary hyperventilation during a certain period of time, maintaining an isocapnea [6]; and threshold valves of pressure loading, which require the individual to perform inspirations or expirations against resistance [7]. This device allows inspirations and expirations to be forced by the device, which causes selective strengthening of the respiratory muscles and mobilizes the entire rib cage. Studies show that therapy with isocapnic voluntary hyperpnea reduces dyspnea and improves exercise capacity and the quality of life of subjects [8]. Currently, the market has electronic IMT valves that seem to provide some benefits in relation to volume increase during training compared to mechanical valves; however, these effects have not yet been clinically demonstrated [9]. There have been, to date, disagreements over the effects of IMT in individuals with COPD [8].

Due to different results on the effect of IMT in COPD subjects, the aim of this study will be to investigate the effects of an IMT protocol to be included in PR programs. The first outcome will be the effects of the training on exercise capacity. Training on inspiratory muscle function (strength and resistance), state of health, and dyspnea level will be considered as secondary outcomes. We believe that the different protocols used in our study are able to guide physiotherapists with regard to the most effective type of IMT, as well as to elucidate the effects of IMT on exercise tolerance, to identify if there is any repercussion on strength and the resistance of the respiratory muscles when subjected to different training types. In addition, the best IMT modality can be included in conventional PR programs, allowing optimization of the therapeutic management of patients with COPD. One also hopes that these results will endorse adjustments to the modalities used to strengthen respiratory muscles, as we believe that a well-implemented therapeutic program can reduce morbidity/mortality rates in these individuals as well as improve their quality of life.

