#### Sample size

The sample size was calculated using two-way analysis of variance (ANOVA) for repeated measures by analyzing walking distance and the standard deviation in meters on the 6MWT from previously published data [15]. A two-tailed alpha error of 0.01 was implemented with a power of 95%, considering clinical improvement for COPD patients after PR and a difference of 30 m between groups on the walking test. For the calculations, the following means and standard deviations of the time observed in the 6MWT in the rehabilitation and control groups were used: pre-PR 312.43 ± 51.26 and post-PR 342.85 ± 48.82 m (rehabilitation group); pre-PR 305.13 ± 54.60 and post-PR 298.20 ± 52.81 m (control group), and a sample size of 32 subjects was found (effect size = 1.04). As the study of Elci et al. [15] was composed of two groups (rehabilitation and controls) and ours will be composed of three groups, we will assume that the 32 subjects will be part of the rehabilitation program (the PRIMTLL and PRIMTIVH groups), and 16 more subjects will be added as a study control group for a total sample of 48 subjects. In addition, 12 more subjects will be added into the study, because we will also assume a 20% loss to follow-up as well as 5% missing data, for a total sample size of 60 subjects.

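### The sample size does not size the arm-versus-arm comparisons that the analysis makes, and Bonferroni on three groups gives up power that a closed test would keep

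*Protocol article*

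**What the plan says.** All from the protocol article.

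- **Statistics analysis:** "two-way ANOVA followed by a Bonferroni post hoc test will be used to compare the differences among the groups". The pairs are not listed. With three groups the natural reading is all three between-arm pairs. The threshold is 0.05 ("The significance level was set at 95"%, with p ≤ 0.05).
- **Sample size:** "A two-tailed alpha error of 0.01 was implemented with a power of 95"%, for "a difference of 30 m between groups on the walking test". The inputs are six-minute walk distances from a published two-group study: "pre-PR 312.43 ± 51.26 and post-PR 342.85 ± 48.82 m (rehabilitation group") and "pre-PR 305.13 ± 54.60 and post-PR 298.20 ± 52.81 m (control group"). The result is 32 subjects at an effect size of 1.04, without saying whether 32 is per group or in total.
- **From two groups to three:** "we will assume that the 32 subjects will be part of the rehabilitation program (the PRIMTLL and PRIMTIVH groups"). Sixteen controls are added to give 48, then 12 more for losses and missing data to give 60.
- **Aim (Background):** to "guide physiotherapists with regard to the most effective type of IMT". This needs a comparison of one IMT arm with the other.

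**The concern.** The stated 95% power comes from a two-group calculation, but the analysis and the aim rest on comparisons between single arms. A reader would take the power to apply to those comparisons. It does not, and no effect is assumed anywhere for one IMT arm against the other.

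The arms are small, about 16 evaluable each, so the choice of pairwise procedure matters. With exactly three groups, dividing alpha by three lowers the power of each comparison when another procedure holds the same family-wise error rate. What is at stake is a missed IMT benefit, or a missed difference between modalities, that the same 60 subjects had a better chance of showing.

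**Working it through.** **1. Reproducing the 32.** Inputs: effect 1.04, two-sided alpha 0.01, power 95%. Normal approximation, n per group = 2(z₀.₉₉₅ + z₀.₉₅)²/d² = 2(2.576 + 1.645)²/1.04² = 32.9, so 33 per group (35 with the t distribution). The stated 32 is therefore close to a *per-group* number. Read as a total (16 per group), it gives only 58% power (t) or 64% (normal). The inflation reproduces: 48/(1 − 0.20) = 60, and 48 × 1.25 = 60.

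**2. The 1.04.** Difference in change = (342.85 − 312.43) − (298.20 − 305.13) = 30.42 + 6.93 = 37.35 m. Over the average SD of about 51.9 m this is 0.72. The post-treatment difference alone gives 44.65 m, or 0.88 SD. A value of 1.04 needs an unstated pre-post correlation of about 0.76: SD of change = 51.9 × √(2 × 0.24) ≈ 36.0 m, and 37.35/36.0 ≈ 1.04. I take 1.04 at face value below and show smaller effects beside it.

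**3. Power of one pair.** Two-sample t-test, noncentrality d√(n/2), degrees of freedom 2n − 2. An equal split of the 48 over three arms is assumed.

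| Effect | n per arm | alpha 0.01 | alpha 0.05/3 | alpha 0.05 |
|---|---|---|---|---|
| 1.04 SD | 16 v 16 | 58% | 66% | 81% |
| 0.88 SD | 16 v 16 | 41% | 49% | 67% |
| 1.04 SD | 20 v 20 (no losses) | 72% | 78% | 89% |

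No cell reaches 95%. At 1.04 SD, 95% for one pair would need 32 per arm (96 evaluable in all) at 0.05/3, or 35 per arm (105) at 0.01.

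**4. Why Bonferroni is not needed for the three pairs.** Let the pairwise nulls be A = B, A = C and B = C. Any two of them together imply that all three means are equal, so every intersection is the global null. A 5% F test of the global null, followed by each pair at 5%, is therefore a closed test. If all means are equal, the F test limits the error to 5%. If exactly two are equal, only one true null pair remains, tested at 5%. This argument fails with four or more groups, and for a family wider than the three pairs.

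**5. Which model term.** With two time points, the group-by-time F test is the one-way F test of change across arms. The simulation is therefore of standardised change scores: 16 per arm, pooled error on 45 df, 100,000 trials per scenario.

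| | F, then pairs at 0.05/3 | F, then pairs at 0.05 |
|---|---|---|
| Power per true pair, 1.04 SD | about 67% | 78% |
| Power per true pair, 0.7 SD | about 31% | 41% |
| Any IMT-versus-sham pair, both arms at 1.04 SD (any pair for the second column) | 82% | 85% |
| Any pair, all means equal | 4.2% | 5.0% |

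Where two arms are equal and the third differs by 1.04 SD, the closed procedure's error for the one true null pair is 4.9% to 5.0%. Testing the pairs at 0.05 *without* the F gate would give 12.0% under the global null, so the gate is essential. The simulated 67% differs slightly from the 66% in step 3 because the error is pooled over three arms.

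**The case against.** The strongest reply is that nothing here is invalid. Bonferroni controls the error over the pairs, and its intervals are simultaneous. The pairs answer both IMT-versus-sham questions and the question of modality. Power given up is a preference, and the gain looks smaller on another measure: with both IMT arms at 1.04 SD, the chance of at least one significant pair rises only from 82% to 85%. The sample size text can also be read as plain arithmetic, 16 per group extended to a third arm (3 × 16 = 48). Naming comparisons and their order is often left to a fuller document.

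Much of this stands. Bonferroni is valid, and the absence of a named deciding comparison in a condensed article is not by itself a fault. What does not fall is the mismatch. If 32 is a two-group total, the stated 95% is wrong for 16 v 16 (58%). If 32 is per group, it has been split over two arms. Neither reading gives the pairs their stated power. The power per comparison also matters, because the conclusion on each modality rests on its own pair.

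A reader might infer two stronger points. One is that the trial's primary test pools the IMT arms against control, so that the pooled and pairwise verdicts could conflict on the same data. The grouping appears only in the sample size reasoning and no pooled analysis is planned, so rates of such conflict would compare the plan with a test it does not contain. The other is that multiplicity is uncontrolled. The Bonferroni step rules that out for the comparisons it covers.

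**Conclusion.** The point holds as a mismatch between sizing and analysis, with an avoidable loss of power. The stated 95% at alpha 0.01 does not apply to any arm-versus-arm comparison. Bonferroni costs roughly 10 percentage points of power per true pair against a closed test with the same 5% family-wise limit.

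This rests on normal data, equal variances, about 16 evaluable subjects per arm, and the effect sizes shown. It also rests on reading the post hoc step as the three between-arm pairs. The closed-test guarantee covers only those three pairs, for one outcome and one model term. It is a change worth making, not an error that undermines the trial.

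**What to change.** **Statistics analysis.** For change in six-minute walk distance, the outcome used for sizing:

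1. Test the three-arm group-by-time term at two-sided 0.05.
2. Only if it is significant, test PRIMTLL v PRWIMT, PRIMTIVH v PRWIMT and PRIMTLL v PRIMTIVH, each at two-sided 0.05 on the pooled error.
3. Keep Bonferroni for any wider family, such as pre-post or per-time-point comparisons.

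**Sample size.** State that the IMT arms are not pooled for the primary test, and that the 95% power at alpha 0.01 does not apply to the pairs. Give their power instead: for 1.04 SD with 16 v 16, about 58% at 0.01, 66% at 0.05/3 and 81% at 0.05. These are single-test figures; with the overall test as a gate, the simulated power per true pair at 0.05 is about 78%.

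**Cost.** Wording only; no added subjects or visits. The pairwise tests then depend on the overall test being significant, and unadjusted pairwise confidence intervals are not simultaneous, which the report should state.

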**Methods:**

This study is a blinded-investigator randomized controlled clinical trial. Sixty subjects will be randomly allocated into three groups: (1) pulmonary rehabilitation (PR) associated with inspiratory muscle training without any load (PRWIMT), (2) PR associated with inspiratory muscle training with a linear load (PRIMTLL), and (3) PR associated with inspiratory muscle training with isocapnic voluntary hyperpnea (PRIMTIVH). The protocol will be performed 5 days a week (3 days with supervision) for 10 weeks. The study will assess anthropometric data, lung function, respiratory muscle strength, and functional capacity by the Incremental Shuttle Walking Test and the Six-Minute Walk Test, lung volumes during the submaximal endurance test, peripheral muscle strength of the upper and lower limbs, dyspnea, and quality of life related to health, before and after the training protocol. Normality will be tested using the Kolmogorov-Smirnov test, and variables will be compared by two-way analysis of variance. The significance level was set at *p* < 0.05. Ethics approval was obtained from the Institutional Ethics Committee in Research (1.663.411). The study results will be disseminated through presentation at specific scientific conferences and publication in peer-reviewed journals.

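### The planned two-way ANOVA has no baseline covariate and does not name its decisive term; ANCOVA on the baseline value would give a modest precision gain at no data cost

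*Protocol article*

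**What the plan says.** The Statistics analysis section of the protocol article states that "two-way ANOVA followed by a Bonferroni post hoc test will be used to compare the differences among the groups", with a two-sided threshold of p ≤ 0.05. The Methods part of the abstract is shorter still: "variables will be compared by two-way analysis of variance". Neither place mentions a baseline covariate, and neither says whether the primary question is answered by the group term, the time term or their interaction.

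The Sample size section is more specific: "The sample size was calculated using two-way analysis of variance (ANOVA) for repeated measures". It lists pre and post 6MWT means and SDs for a rehabilitation and a control group, and targets "a difference of 30 m between groups on the walking test". The two factors are therefore presumably group (three arms) and time (before, after).

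Under Study design, the initial evaluation takes place before randomisation, so a baseline value is planned for every randomised subject.

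**The concern.** In a randomised pre/post design the treatment effect is a difference that appears only after training. A two-way ANOVA on group and time offers three terms, and only the interaction estimates that difference directly. The group main effect averages the pre-training difference, which is zero in expectation, with the post-training one. A plan that speaks only of comparing groups leaves the choice of term open.

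Even the right term leaves precision unused. The interaction subtracts the whole baseline value, whereas ANCOVA subtracts only the part that predicts the outcome. With about 16 evaluable subjects per arm, precision is scarce and the covariate is already collected.

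The post hoc step adds to the openness. Bonferroni could run over 3 between-arm pairs or over all 15 pairs of the six group-by-time cells (6 × 5 / 2). The 15 pairs include within-arm pre-post comparisons. All three arms receive full rehabilitation, so such comparisons say little about which training modality is better.

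**Working it through.** **The plan's own figure.** The article gives 32 subjects for effect size 1.04, two-sided alpha 0.01 and 95% power. A two-sample calculation with these inputs gives 33 per arm (normal) or 35 per arm (t), so 32 is not reproduced as a two-arm total. That is a separate issue. The article states no power for the analysis that it describes, so power is computed here.

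**Inputs from the Sample size section.**
- Target difference D = 30 m.
- 16 evaluable subjects per arm (48 in total over three arms).
- SD S = root mean square of the four printed SDs: √[(51.26² + 48.82² + 54.60² + 52.81²)/4] = 51.9 m.

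**Assumed.** Pre-post correlation ρ = 0.5 to 0.8, which the article does not give, and equal baseline means in expectation.

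**SD of each analysis quantity.**
- Group-by-time interaction (difference in change): effect D, SD = S√[2(1−ρ)].
- ANCOVA on baseline: effect D, SD = S√(1−ρ²).
- Group main effect (average of pre and post): effect D/2, SD = S√[(1+ρ)/2].

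**Variance ratio.** ANCOVA to change score = (1−ρ²)/[2(1−ρ)] = (1+ρ)/2, which is 0.75 at ρ = 0.5 and 0.90 at ρ = 0.8. A change-score analysis would need 16/0.75 = 21.3 or 16/0.90 = 17.8 per arm to match ANCOVA with 16.

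**Standardised effects (ρ = 0.5; ρ = 0.8).**
- Interaction: 30/51.9 = 0.58; 30/32.8 = 0.91.
- ANCOVA: 30/44.9 = 0.67; 30/31.1 = 0.96.
- Main effect: 15/44.9 = 0.33; 15/49.2 = 0.30.

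**Power for one between-arm comparison (noncentral t, 30 df).**

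| Term tested | alpha 0.05, ρ 0.5 to 0.8 | alpha 0.05/3, ρ 0.5 to 0.8 |
|---|---|---|
| Interaction (change score) | 35% to 71% | 20% to 53% |
| ANCOVA | 45% to 75% | 28% to 58% |
| Group main effect | 15% to 13% | 7% to 6% |

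**Sensitivity.** With the pooled post-training SD of 50.9 m, a normal approximation and alpha 0.05, the interaction gives 39%, 58% and 96% at ρ = 0.5, 0.7 and 0.9. ANCOVA gives 49%, 65% and 97%. The gain is about 10, 7 and 1 points, so it fades as the correlation rises.

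**The three terms on the printed means.** The baseline difference is 312.43 − 305.13 = 7.30 m and the post difference is 342.85 − 298.20 = 44.65 m. The interaction is 44.65 − 7.30 = 37.35 m, and the main effect is (7.30 + 44.65)/2 = 25.98 m.

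**The case against.** A reader might infer from the phrase about comparing groups that the group main effect is the primary test, and so that the plan halves its own effect. The article does not support this. It never designates the main effect, and the Sample size section's reference to repeated measures with pre and post means points to a group-by-time analysis. The interaction uses the baseline value and does not dilute the effect. The 13-15% power at alpha 0.05 is a conditional worst case, not a property of the plan.

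A reader might also infer an unpaired ANOVA, because the Statistics analysis section and the abstract omit the words on repeated measures. Ignoring the pairing would inflate the interaction's standard error by 1/√(1−ρ), or 1.4 to 2.2 times. The omission is more plausibly abbreviation.

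Chance baseline imbalance should not be overplayed either. Its standard error between two arms is 51.9 × √(2/16) = 18.3 m, but a change score is unbiased over randomisations. Given an imbalance of one standard error, it shifts by only (1−ρ) times that: 9.2 m at ρ = 0.5 and 3.7 m at ρ = 0.8.

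Finally, a condensed article may leave the decisive term, covariates and the post hoc family to a fuller document. That stands for the missing detail taken alone. It does not remove the point, because the article does fix a method, and a better one is available from data already planned.

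**Conclusion.** The point holds as a free improvement of modest size. On the likeliest reading the planned test is valid but less efficient than ANCOVA. At 30 m, SD 51.9 m and 16 per arm, the gain is roughly 4 to 9 power points at alpha 0.05 and 5 to 7 at 0.05/3 over ρ = 0.5 to 0.8, and about 1 point at ρ = 0.9. These figures rest on the assumed correlation and on equal variances before and after training. The article also leaves the decisive term unnamed. That matters because one available choice, the group main effect, would have very little power. Nothing shows that this choice is intended. The difference between the alpha used for sizing (0.01) and the one used for analysis (0.05), and the question of which walking test is primary, are separate matters.

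**What to change.** Replace the ANOVA sentence with a short paragraph along these lines. The post-training value of 6MWT distance, the outcome used for sizing, is analysed by ANCOVA with allocated group as factor and the baseline value as covariate. The three between-arm differences are reported with confidence intervals and Bonferroni adjustment over those three comparisons. The other continuous outcomes use the same model. Within-arm pre-post tests are descriptive only.

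If the sponsor prefers to keep the ANOVA, the minimum is to state that it is a repeated-measures model and that the group-by-time interaction is the decisive term, and to define the Bonferroni family.

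The cost is one paragraph, slightly more analysis work and possibly another package if the named software does not fit the model. No new data are needed. Naming 6MWT here follows the sizing and does not settle which walking test is the primary outcome.

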#### Dissemination

The results found in this study will be presented in specific scientific conferences and will be submitted for publication in peer-reviewed journals.

## Discussion

Literature data reporting the effects of respiratory muscle training regarding exercise tolerance are rare nowadays. We believe that the different protocols used in our study of high load and low load training will be able to guide respiratory therapists to the most effective respiratory muscle training type. Moreover, the study will elucidate the effects of IMT on exercise tolerance, identifying if there is any repercussion on both respiratory muscle static pressure and respiratory muscle strength when the patient is subjected to different efforts.

Finally, the best IMT modality may be included in conventional PR programs, thus optimizing the therapeutic management of COPD patients. We also hope that these findings endorse adjustments to the modalities used for respiratory muscle strengthening, as we believe that a well-implemented therapeutic program may reduce the morbidity/mortality rates for these individuals as well as improve their quality of life.

The protocol performance may show some limitations as individuals’ adherence and subjects’ access to the hospital will vary. Such limitations will be controlled by free specialized medical service and by the provision of a free bus pass allowing subjects to attend the interventions at the PR service. As clinical limitations we may highlight COPD exacerbation and/or other general clinical issues that may lead to a subject’s absence of 3 or more consecutive days or subjects being withdrawn from the study.

### Trial status

The trial is currently in recruitment phase at the Ambulatory Pulmonology department of University Hospital Onofre Lopes (HUOL)/Empresa Brasileira de Serviços Hospitalares (EBSERH). Recruitment will begin in July 2019, and the protocol is expected to finish in June 2020.

## Abbreviations

1RM: 1 maximal repetition
6MWT: Six-Minute Walk Test
ATS/ERS: American Thoracic Society/European Respiratory Society
CAT: COPD Assessment Test
CONSORT: Consolidated Standards of Reporting Trials
COPD: Chronic obstructive pulmonary disease
EBSERH: Empresa Brasileira de Serviços Hospitalares
FEV_1_: Forced expiratory volume in the first second
FVC: Forced vital capacity
GOLD: Global Initiative for Chronic Obstructive Lung Disease
HUOL: University Hospital Onofre Lopes
IMT: Inspiratory muscle training
PRIMTIVH: PR associated with inspiratory muscle training through isocapnic voluntary hyperpnea
PRIMTLL: PR associated with inspiratory muscle training with linear load
ISWT: Incremental Shuttle Walking Test
MEP: Maximal expiratory capacity
MIP: Maximal inspiratory pressure
mmHg: Millimeters of mercury
mMRC: Modified Medical Research Council
OEP: Optoelectronic plethysmography
PR: Pulmonary rehabilitation
PRWIMT: PR associated with inspiratory muscle training without any linear load
RR: Respiratory rate
RV: Residual volume
SAP: Systemic arterial pressure
SNIP: Sniff nasal inspiratory pressure
SPImax: Sustained maximum inspiratory pressure
SPIRIT: Standard Protocol Items: Recommendations for Interventional Trials
SpO_2_: Peripheral oxygen saturation
TLC: Total lung capacity
WHO: World Health Organization
Wmax: Maximum work
